### 5.3 Other Outcomes of Interest

Not applicable.

### 5.4 Safety Outcomes

Safety is the primary outcome of this trial (see section **5.1 Primary Outcome**).

## 6. STUDY DESIGN

### 6.1 General study design and justification of design

This trial is a phase I interventional trial consisting of a dose escalation part (1) and a dose consolidation part (2):

- 1- A single ascending dose part in 3 patients for up to 14 weeks plus a follow-up 4 weeks after the last infusion.
- 2- A repeated dose administration part in 9 patients for up to 8 weeks plus a follow-up 4 weeks after the last infusion.
- 3- Optional: The 3 patients from part 1, if they wish, could continue their treatment beyond the planned final assessments for up to 8 weekly TLN infusions.

[figure not shown]

All data will be analysed in a descriptive manner in order to collect first clinical data with this new liposomal formulation of GM1.

#### 6.1.1 Dose escalation (Part 1)

In this part a group of 3 patients will receive a single weekly dose that will be increased according to the schedule defined. In parallel, meaning that the first patient will receive a dose X on week Y, if the safety assessment is positive (see **Section 8.3 Dose modifications**) then the following week (Y+1) this patient will receive the next dose (X+1), on that week (Y+1) two other patients will receive the same dose X to confirm the safety assessment. *In fine*, every week patient 1 will receive one dose at the same time that patients 2 & 3 receive the preceding dose.

This weekly increase has been elected to allow rapid determination of the MSD and rapidly reach a dose level that will be beneficial for the patients involved in this trial. This is allowed by the fact that GM1 is expected to be safe and no clear AE are foreseen within this dose range. Furthermore, the 1 + 2 pattern allows one week observation of each dose increase in 1 patient before infusing 2 more.

The first dose level starts at 6 mg which will increase to 12 and 60 mg, then increasing by equal steps of 60 mg up to 720 mg. The escalation will be stopped individually according to the decision matrix detailed in the **Section 8.3 Doses modifications**. The three first steps of the dose are purposely low to account for any possible unexpected effects of the formulation.

Throughout the escalation part, all patients will be monitored twice weekly to record AEs and document them. Monitoring will take place once before each TLN infusion (beginning of the week) and a second time by the end of each week (performed by the principal investigator) to collect AE and allow enough time for the IMC to review them and take their decision on the next infusion/dose modification/delay.

At the end of the escalation, the average of the three maximum tolerated doses by the three patients will be defined as MSD for part 2. With this design, we aim to find the highest dose that generates, if any at all, at maximum only transient mild/moderate AEs. At the same time, this will allow to glean information on clinical effect for the planning of a potential phase II study.

If a patient drops out for reasons unrelated to the drug treatment, this patient will be replaced. The three MSD are necessary to establish the dose that will be used for the multiple dose administration. This is a design that allows fast escalation with minimal risks for the patients since the dose steps are small, the starting dose is very low and each increment is split in a 1 + 2 pattern. With N=3 we expect to show evidence of common AEs inherent to the TLN formulation. This design (part 1) lacks the assessment of mid-term cumulative effects of the drug at a constant dosage. Therefore, an additional phase (part 2) will be performed to complete the safety profile under constant weekly dosages and provide more insight of the tolerability over 8 repeated doses.

#### 6.1.2 Dose consolidation (Part 2)

The MSD will then be administered repeatedly (8 times over 8 weeks) to 9 additional patients to consolidate what will be found in the escalation part.

At the first infusion, blood will be recovered for PK analysis over 96 h (see **Section 9.2.2 Assessment of Secondary Outcomes**). The expected half-life is projected to be 30 h (extrapolation from pre-clinical studies). Therefore, 96 h would suffice to obtain 3 half-life periods and to observe enough tapering.

Throughout this part 2, all patients will be monitored weekly to record AE and document them. The clinical and PD assessment will be performed similarly to the dose escalation. This part will provide more information on the tolerability of the chosen MSD over repeated injections. This will complete the safety profile while avoiding to mobilize the whole cohort of patients for the dose escalation. This is still a modest number of patients but this will suffice to evidence the most common AEs associated with the treatment. Moreover, potential clinical effects on signs and symptoms of PD can be studied in view of the planning of a phase II study.

In this multiple dose administration part, patients that drop out for reasons unrelated to the treatment with TLN will be replaced due to the small number of patients involved.

#### 6.1.3 Continued TLN infusions

Patients wishing to continue their treatment beyond the assessments in part 1 of the trial described above, can receive further weekly TLN infusions for up to 8 additional weeks at their personal MSD or at the dose level 14. A lighter schedule (one instead of two visits per week) than part 1 was elected for the patients' convenience. All patients will be monitored weekly to record AE and assessed based on details given in chapter **9. ASSESSMENTS**.

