#### Part 1 – Dose Escalation:

The drug will be administrated in a single ascending dose (SAD) as a once weekly i.v. infusion in 3 patients up to 14 dose levels or until unacceptable toxicity appears (see section **6.1.1 Dose escalation** for details on the sequence between patient 1 and 2/3).

The aim of this dose escalating procedure is to define the MSD in terms of the occurrence of AEs dependent on their seriousness, intensity and causality according to the standards and definitions given in this trial protocol (see section **8.3 Doses modifications**).

|               |        |
|---------------|--------|
| Dose level 1  | 6 mg   |
| Dose level 2  | 12 mg  |
| Dose level 3  | 60 mg  |
| Dose level 4  | 120 mg |
| Dose level 5  | 180 mg |
| Dose level 6  | 240 mg |
| Dose level 7  | 300 mg |
| Dose level 8  | 360 mg |
| Dose level 9  | 420 mg |
| Dose level 10 | 480 mg |
| Dose level 11 | 540 mg |
| Dose level 12 | 600 mg |
| Dose level 13 | 660 mg |
| Dose level 14 | 720 mg |

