- Non-Motor Symptoms Questionnaire (NMSQuest): This questionnaire enables clinicians to complete a comprehensive assessment of a diverse range of non-motor symptoms which can occur in all stages of PD. It is a patient-based screening tool designed to draw attention to the presence of non-motor symptoms in patients for further investigation or treatment. Patients will be asked to give their answer ("ja" or "nein") to 30 questions.
- Levodopa equivalent daily dose (LEDD): LEDD will be assessed at each visit and will be calculated according to Verber *et. al*.
- Pharmacokinetics (PK) of total GM1 in blood over the first 96 h after the first infusion (only in part 2 of the trial):  
The assessment of PK will be determined by the calculation of the Maximum Observed Drug Concentration ( $C_{max}$ ) in plasma, the Time of Maximum Drug Concentration ( $T_{max}$ ) in plasma,  $AUC_{inf}$  in plasma, half-life ( $t_{1/2}$ ) Clearance (CL) and the volume of distribution ( $V_d$ ).  
The predicted half-life of the drug is 30 h according to our pre-clinical data obtained in animals. The blood collection for PK will therefore be performed at the following timepoints after the first infusion (only part 2 of the trial):
  - 0 min (right before the infusion, pre-dose)
  - 5 min before the end of the infusion
  - 30 min after infusion
  - 1 h after infusion
  - 4 h after infusion
  - 24 h after infusion
  - 48 h after infusion
  - 72 h after infusion
  - 96 h after infusion
 Instructions for the collection of blood and the processing and handling are provided in **Annex 3**).
- Determine the maximal suitable dose (MSD): MSD is calculated as the average dose from all maximally reached doses by the 3 patients in the dose escalating part of this trial.

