### **9.3.11 Visit 8 – 14: Treatment (days 8, 15, 22, 29, 36, 43 & 50)**

- Vital signs
- Full lab tests
- MSD infusion of TLN
- MDS-UPDRS (Part III before the infusion; Part I, II and IV during the infusion; Part III again after the infusion)
- NMSQuest
- LEDD
- AE recording

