**After dose escalation: optional further treatment**

9.3.14 Visit 0: "Re-consent" (day 0)

- Explanation of the option of treatment prolongation (15 min).  
Patient information is handed out in writing. This procedure might also take place during the final assessment or follow-up visit of part 1. Then this visit will not take place.

9.3.15 Visit 1-8: Treatment (day 1, 8, 15, 22, 29, 36, 43 & 50)

- Vital signs
- Full lab tests
- MSD Infusion of TLN
- MDS-UPDRS (Part III before the infusion; Part I, II and IV during the infusion; Part III again after the infusion)
- NMSQuest
- LEDD
- AE recording

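### The protocol uses MSD in two senses (personal dose and three-patient average) and builds it from two inputs (tolerated and reached doses), so the extension dose and the Part 2 dose lack a single reading

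*Protocol*

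**What the plan says.** Four places in the protocol bear on the extension dose.

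- Section 6.1.3 sets it: Part 1 patients "can receive further weekly TLN infusions for up to 8 additional weeks at their personal MSD or at the dose level 14".
- Section 9.3.15, the procedure list for extension treatment visits 1 to 8, reads "MSD Infusion of TLN". It does not say personal, does not mention level 14 and does not refer back to 6.1.3. Part 2 uses the same phrase in 9.3.9 and again in 9.3.11 ("MSD infusion of TLN"), where it means the common Part 2 dose.
- Section 9.2.2 gives the calculation rule: "MSD is calculated as the average dose from all maximally reached doses by the 3 patients".
- Section 6.1.1 gives a similar rule with a different input and a stated scope: "the average of the three maximum tolerated doses by the three patients will be defined as MSD for part 2".

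Section 6.1.1 also uses the term per patient: "The three MSD are necessary to establish the dose that will be used for the multiple dose administration". The term personal MSD is not defined anywhere.

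Two statements of aim bear on the input. Section 6.1.1 seeks "the highest dose that generates, if any at all, at maximum only transient mild/moderate AEs", and the Part 1 text in section 8.1.1 says that the procedure is meant "to define the MSD in terms of the occurrence of AEs dependent on their seriousness, intensity and causality".

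**The concern.** TLN had no prior clinical data when this was written (section 3.4), and section 6.1.1 itself notes that Part 1 does not assess cumulative effects at a constant dose. The extension is constant weekly dosing, up to 8 infusions, in those same Part 1 patients. Its dose should have one reading.

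Two things prevent that. First, one abbreviation stands both for a patient's own value and for the average of three patients, and the extension visit list does not say which applies. Second, the average itself has two inputs. Under the section 8.3 table for Part 1, a possibly related grade 3 event, for example, stops the patient at the dose just given. That dose has been reached but not tolerated. If 9.2.2 is followed literally, a dose that triggered a stop enters the Part 2 dose given to nine further patients, and it could also be taken as that patient's personal value.

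**Working it through.** The protocol states no figure to reproduce here: section 11.2 says the sample size was not formally calculated, and no worked MSD is given. The check compares the readings on the dose ladder in section 8.1.1: 6, 12 and 60 mg, then steps of 60 mg up to 720 mg at level 14. The patients' maxima below are assumed for illustration.

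**Personal value against average.** Average = (d1 + d2 + d3) / 3, where each d is one patient's highest dose. Unless all three are equal, at least one patient lies below the average.

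| Assumed maxima (mg) | Average (mg) | Average / lowest maximum |
|---|---|---|
| 720, 720, 720 | 2160/3 = 720 | 1.00 |
| 720, 720, 660 | 2100/3 = 700 | 700/660 = 1.06 |
| 720, 720, 480 | 1920/3 = 640 | 640/480 = 1.33 |

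Under 6.1.3 the third patient would receive 660 mg in the second row and 480 mg in the third. Under 9.3.15 read with 9.2.2, that patient would receive 700 mg or 640 mg. The other two patients would be dosed below their own 720 mg.

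**Reached against tolerated.** Suppose a patient is stopped by toxicity at level k, having tolerated level k − 1.

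- Difference for that patient: dose(k) − dose(k − 1) = 60 mg for every k from 4 (120 − 60) to 14 (720 − 660).
- Effect on the Part 2 average: 60/3 = 20 mg for each such patient.
- Stop at level 9, others at 720 mg: reached gives (420 + 720 + 720)/3 = 620 mg; tolerated gives (360 + 720 + 720)/3 = 600 mg.
- Stop at level 14, others at 720 mg: reached gives (720 + 720 + 720)/3 = 720 mg; tolerated gives (660 + 720 + 720)/3 = 700 mg.

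If nobody is stopped, the two inputs coincide.

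**The case against.** The best reply is that the intent can be recovered. Section 6.1.3 is the specific rule for the extension, while 9.3.15 is a procedure checklist with no dose in mg, and the prolongation schedule table simply lists an infusion. Section 6.1.1 limits the average to Part 2 and speaks of three MSDs, so the bare term in 9.3.15 is probably shorthand for the personal value. The natural sense of 6.1.3 is the personal value for a patient whose escalation stopped early and level 14 for one who completed it, not a free choice. The aims in 6.1.1 and 8.1.1 point to the tolerated dose.

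Safeguards also apply. Under section 1.6 the Internal Monitoring Committee meets in principle weekly, and its decision to continue each patient must be unanimous and includes an independent physician. Under section 1.7 the DSMB meets once the MSD is defined.

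Most of this stands. It shows what the authors meant and why a wrong dose is unlikely. It does not make the sections agree: the calculation rule in 9.2.2 names neither the personal value nor the tolerated dose, and the committee still needs the protocol to tell it which dose is specified.

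A reader might infer that the plan directs extension patients to be dosed above what they tolerated, perhaps by a large multiple. The documents do not support that. It requires the general definition in 9.2.2 to override the specific rule in 6.1.3. Large multiples further require a patient stopped far below the others to enter the extension despite the withdrawal criteria in 7.3, the completion condition in 2.7 and the committee's unanimous decision.

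**Conclusion.** The inconsistency is real but minor. The extension dose is stated as personal in 6.1.3 and, by the 9.2.2 definition, as an average in 9.3.15. The average is built from tolerated doses in 6.1.1 and from reached doses in 9.2.2.

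The first conflict concerns at most three patients in an optional phase and arises only if their maxima differ. In the two illustrations the excess is 40 mg (700 against 660) and 160 mg (640 against 480). The second arises only if a patient is stopped by toxicity, and it shifts the Part 2 dose by 20 mg for each patient stopped at level 4 or above. If all three tolerate 720 mg, every reading gives 720 mg.

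These sizes rest on assumed maxima and on the level below a stop having been tolerated. They describe how far the readings diverge and say nothing about how likely a wrong dose is.

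**What to change.** Three wording changes:

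1. In 9.3.15, replace the infusion line with: *TLN infusion at the patient's personal MSD (section 6.1.3)*.
2. In 9.2.2, replace *maximally reached* with *maximum tolerated*, so that it matches 6.1.1 and the Part 2 dose has one input.
3. In 6.1.1 or 6.1.3, define the personal MSD as the highest Part 1 dose level the patient received that did not itself trigger a stop under section 8.3 for that patient. This is 720 mg if level 14 was tolerated. A patient stopped at level 1 has no tolerated level and does not enter the extension.

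The cost is one line in 9.3.15, one phrase in 9.2.2 and one short definition. No patients, visits or procedures are added.

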## **6.2 Methods of minimising bias**

### **6.2.1 Randomisation**

Not applicable.

### **6.2.2 Blinding procedures**

Not applicable.

### **6.2.3 Other methods of minimising bias**

For the primary endpoint, the assessments of the outcome are based on standards and norms. In this trial, the following validated instruments will be used to assess secondary endpoints: MDS-UPDRS, PDQ-39, ESS, NMSQuest, SAS, BDI, and MoCA.

## 7. STUDY POPULATION

### 7.1 Eligibility criteria

Participants fulfilling all of the following inclusion criteria are eligible for the trial:

1. Informed consent as documented by signature.
2. Male and female subjects, aged 40 to 80 years.
3. Confirmed Parkinson's disease according to British brain bank criteria.
4. Hoehn and Yahr Stage 0 – 2.5 on medication.
5. Stable PD treatment for 4 weeks at least.
6. Absence of dementia confirmed by cognitive testing (MoCA >25).

The presence of any one of the following exclusion criteria will lead to exclusion of the participant:

1. Contraindications to the class of drugs under study, e.g., known hypersensitivity or allergy to class of drugs or the investigational product.
2. Women who are pregnant or breast feeding, or planning to become pregnant during the course of the trial or in the 12 weeks following the trial.
3. Lack of safe contraception, defined as:
  - Female participants of childbearing potential, not willing to use double method of contraception (hormonal and mechanical) for the entire study duration. Female participants who are surgically sterilised / hysterectomised or post-menopausal for longer than 2 years are not considered as being of child bearing potential.
  - Male participants, not using and not willing to using a medically reliable method of contraception for the entire study duration, such as condoms or who are not using any other method considered sufficiently reliable by the investigator in individual cases.
4. Other clinically significant concomitant disease states (e.g., renal failure, hepatic dysfunction, cardiovascular disease etc.) that are not under stable control.
5. Known or suspected non-compliance, drug or alcohol abuse.
6. Inability to follow the procedures of the trial, e.g., due to language problems, psychological disorders etc. of the participant.
7. Participation in another trial with an investigational drug 4 weeks prior to the present trial.
8. Previous enrolment into the current trial.
9. Enrolment of the investigator, his/her family members, employees and other dependent persons.
10. Subject has an atypical parkinsonian syndrome or secondary parkinsonism.
11. Patients with comorbidity that may interfere with the course of the trial.
12. Patients who are not considered to be eligible to participate in clinical trial by the investigator.

### 7.2 Recruitment and screening

The patients will be identified by the PI according to the inclusion/exclusion criteria. If a patient is willing to participate in the trial, the informed consent procedure will thereafter be performed. Patients will be informed orally and in writing, that pre-screening assessments need to take place before enrolment into the trial. If patients do not meet these pre-screening criteria, they will be judged as screening failures. Patients will have up to 28 days of time to take their decision on whether to participate in the trial.

### 7.3 Criteria for withdrawal / discontinuation of participants

Patients will be withdrawn from the trial for any of the below listed reasons:

- Unacceptable toxicity as described in section **8.3 Dose modifications**
- Protocol treatment has to be delayed for more than 3 weeks
- Patient refuses further treatment
- Patient becomes pregnant
- Medical judgement by the treating physician
- Severe non-compliance with the trial protocol

For data and follow-up, see section **8.5 Data Collection and Follow-up for withdrawn participants**.

## 8. STUDY INTERVENTION

### 8.1 Identity of Investigational Products and administration

#### 8.1.1 Experimental Intervention treatment

Talineuren is a liposomal formulation of GM1 ganglioside. The liposome acts as carrier for GM1 and is composed of cholesterol and sphingomyelin. For further information on the formulation of the IMP, please consult the current IB.

The experimental treatment with TLN consist of two parts:

#### Part 1 – Dose Escalation:

The drug will be administrated in a single ascending dose (SAD) as a once weekly i.v. infusion in 3 patients up to 14 dose levels or until unacceptable toxicity appears (see section **6.1.1 Dose escalation** for details on the sequence between patient 1 and 2/3).

The aim of this dose escalating procedure is to define the MSD in terms of the occurrence of AEs dependent on their seriousness, intensity and causality according to the standards and definitions given in this trial protocol (see section **8.3 Doses modifications**).

|               |        |
|---------------|--------|
| Dose level 1  | 6 mg   |
| Dose level 2  | 12 mg  |
| Dose level 3  | 60 mg  |
| Dose level 4  | 120 mg |
| Dose level 5  | 180 mg |
| Dose level 6  | 240 mg |
| Dose level 7  | 300 mg |
| Dose level 8  | 360 mg |
| Dose level 9  | 420 mg |
| Dose level 10 | 480 mg |
| Dose level 11 | 540 mg |
| Dose level 12 | 600 mg |
| Dose level 13 | 660 mg |
| Dose level 14 | 720 mg |

#### Part 2 – Dose consolidation:

As soon as the MSD is defined, 9 patients will receive the full MSD in the multiple dose administration part once a week for 8 weeks.

#### 8.1.2 Control Intervention

Not applicable

#### 8.1.3 Packaging, Labelling and Supply (re-supply)

Talineuren will be supplied as a white translucent solution prefilled in labelled glass vials with rubber stoppers. Each vial is packaged in a labelled cardboard box.

Talineuren will be provided free of charge by the sponsor and manufacturer InnoMedica AG Schweiz. Distribution to the site will be handled directly by InnoMedica Schweiz AG. An initial stock will be provided upon site activation. Thereafter, the site will be responsible for ordering additional TLN. The completed IMP order form (provided in ISF during initiation) should be sent to [REDACTED] no later than one working week prior to desired date of receipt.

Talineuren will be shipped temperature-controlled at temperatures between 2-8°C. For further details, please see the information on drug supply, handling and IMP deviations guideline.

Talineuren labels contain information to meet the applicable regulatory requirements. The investigational products will be labelled and handled as open-label material. Label sample is provided here below:

#### 8.1.4 Storage Conditions

##### 8.1.4.1 Storage before dilution

Talineuren is a sterile solution for i.v. infusion. The vials are for single use and must not be stored once opened. Talineuren must be stored at temperatures between 2-8°C. Storage area temperature conditions must be monitored and recorded.

Keep vial in cardbox until dilution.

In case the vial or the rubber stopper has been damaged, or any visible particles or sediments are in the vial, put the IMP in quarantine, complete a product quality complaint form and notify InnoMedica [REDACTED] immediately. For further details, please see the information on drug supply, handling and IMP deviations guideline.

Do not use vials after the retest date printed on each vial.

